## Abstract

**Background:**

Severe chronic constipation (SCC) is a common functional gastrointestinal (GI) disorder associated with disruptions in GI motility. Abnormalities between gut microbiota and microRNAs (miRNAs) are implicated in the pathogenesis of GI motility in SCC. Acupuncture has been shown to improve constipation-related symptoms and rebalance the gut microbiota. This protocol proposed a plan to explore the hypothesis that the efficacy of acupuncture is associated with the crosstalk between gut microbes and miRNAs in patients with SCC.

**Methods:**

This trial is designed as a randomized, sham-controlled trial involving 80 patients and 40 healthy volunteers. A total of 80 patients with SCC (≤2 mean spontaneous, complete bowel movements per week [CSBMs]) will be randomly allocated to receive either 16-session acupuncture at true acupoints or non-penetrating sham acupuncture at non-acupoints for 4 weeks. The primary outcome will be the proportion of patients with ≥3 mean weekly CSBMs over weeks 1–4 and 5–8. Secondary efficacy endpoints include bowel movements, stool consistency, degree of straining, and the quality of life. Healthy volunteers will not receive any clinical intervention. Fasting plasma and fecal samples will be analyzed by 16S rRNA third-generation sequencing and miRNA high-throughput sequencing technologies. Finally, a tripartite network analysis will be used to investigate the interactions among clinical efficacy, miRNAs, and intestinal microbiota.

**Discussion:**

From the perspective of microRNA-gut microbiota regulatory mechanisms, our results will partially illuminate the crucial role of fecal miRNAs and intestinal microbiota to understand how acupuncture exerts its anti-constipation role.

**Trial registration:**

This trial is registered with ChiCTR2100048831, registered 18 July 2021; ethical approval has been obtained from the Sichuan Regional Ethics Review of Committee on Traditional Chinese Medicine, approval ID: 2021KL-023.

## Introduction

Chronic constipation refers to a functional bowel disorder except for irritable bowel syndrome (IBS), in which symptoms of difficult, infrequent, or incomplete defecation predominate (1). It affects ~14% of the population worldwide, with a prevalence of 4–6% in China (2, 3). Health-related quality of life (QOL) is negatively affected by the presence of chronic constipation and by its severity (4, 5). Severe chronic constipation (SCC) has distinct duration and severity of symptoms over mild and transient types, generally associated with weekly spontaneous bowel movements (SBMs) of <2 times (6). Even though empirical laxatives are the mainstay for constipated patients, a high level of dissatisfaction has been reported since they often target only 1 aspect of the disease (7). In addition, relief of symptoms is limited to the period of treatment, and efficacy tends to fade after the drug is discontinued (8). One European survey of chronic constipation revealed that almost half were using alternative treatments (acupuncture, cupping, and homeopathy), and nearly 90% of respondents expressed interest in new therapies (9).

Acupuncture is the representative of non-pharmaceutical choice with eminent advantages in the management of SCC. Our previous study revealed that the effectiveness of acupuncture was non-inferior to mosapride in increasing the weekly SBMs, but with a better safety profile (10). The effects of acupuncture could accumulate with 4-week treatments and persist throughout the 4-week follow-up. In addition to the improvement of intestinal discomforts, acupuncture can also bring better QOL to SCC patients with improved mental symptoms such as anxiety and depression (4, 11–13). Gastrointestinal (GI) motor function abnormalities are considered to be of primary importance for SCC symptoms generation. Previous basic researches demonstrated that acupuncture stimulation could improve GI motility, promote contractility of colonic tissue, and facilitate gut transit in constipated animals (14–16). However, the detailed mechanisms underlying acupuncture for SCC remain largely unknown.

Intestinal microbiota plays a critical role in GI transit. Following the onset of SCC, in addition to the decreased richness and diversity of the intestinal microbiome, microbial metabolites vary greatly (17). For example, metabolites short-chain fatty acids and γ-aminobutyric acid decrease, leading to reduced expression of the colonic serotonin transporter and intake of 5-hydroxytryptamine (5-HT), which weakens intestinal motility (18). Additionally, intestinal neuroendocrine factors may also be changed through the release of bacterial endotoxin lipopolysaccharide and bacterial final metabolites, resulting in the aggravation of constipation symptoms (19, 20). In a previous study, we have demonstrated that acupuncture could affect the production and degradation of short-chain fatty acids mainly by promoting the recovery of intestinal microbiome, thus stimulating the neural signal transduction of 5-HT signal pathway (21). Besides, acupuncture was found to be lesser effective when the intestinal microbial community was dysregulated by antibiotics (22). Nevertheless, the behind mechanism has not been clarified yet.

MicroRNA (miRNA) is a kind of endogenous, non-coding single-stranded RNA with a length of about 22 nucleotides and is highly conserved during evolution (23). It is proven that miRNA along with its related networks is involved in the imbalance of intestinal microbiota, which is the key to the pathogenesis of functional constipation (24–27). For instance, in patients with SCC, 13 miRNAs were found to be up-regulated in colonic mucosa and were identified as biomarkers for the diagnosis of disease severity (24). The miRNAs which show differential expression patterns could cause changes in intestinal microbial metabolic pathways via targeting and regulating the transcriptional levels of related genes (25, 26). In an animal experiment, related miRNA deficiency was highly likely to cause intestinal microbial disorders, while fecal miRNA transplantation could reshape the microbiota and alleviate gastrointestinal symptoms (27).

Some studies have shown that the therapeutic effect induced by acupuncture might be correlated with the regulatory mechanism of miRNAs (28–30). However, there is no report on whether the treatment of SCC by acupuncture involves the miRNA-intestinal microbiota crosstalk. Hence, a randomized, sham-controlled trial will be conducted to explore the interactions among the efficacy of acupuncture, changes of fecal miRNA, and the intestinal microbiota. In all, our study will provide initial support for the role of alternations in the microRNA-gut microbiota crosstalk during the symptom improvement induced by acupuncture.

## Methods

### Objectives

This trial aims to (1) re-evaluate the pure therapeutic effect of acupuncture for SCC; (2) identify the correlation between the gut microbiota and fecal miRNAs in patients with SCC; and (3) investigate the interactions among acupuncture-induced improvement of constipation symptoms, changes of fecal miRNAs and regulation of intestinal microbiota.

### Trial Design

This trial is designed as a randomized, sham-controlled trial with blinded participants, outcome assessor, and statistician. In this study, 80 eligible participants will be randomized to the verum acupuncture (VA) or sham acupuncture (SA) group with a ratio of 1:1. The total research period will be preceded by a 1-week run-in phase after the screening visit, then following the 4-week treatment phase, and 4-week follow-up phase. Forty healthy volunteers will also be enrolled to serve as a healthy control group. Healthy volunteers will not receive any treatment, and the correlation between gut microbiota and fecal miRNAs will be determined by comparing the constipated patients before treatment with them. The time frame of this trial is presented in Table 1.

**Table 1 T1:** Time points of treatment assessment.

	**Enrollment**	**Baseline**	**Treatment phase**		**Follow-up phase**			
**Time point**	**Week −1**	**Week 0**	**Week 2**	**Week 4**	**Week 5**	**Week 6**	**Week7**	**Week 8**
**Screening and enrolment**
Clinical interview	**×**							
Laboratory test	**×**			**×**				
Gut microbiota analysis	**×**			**×**				
MicroRNAs analysis	**×**			**×**				
Eligibility screen	**×**							
Informed consent	**×**							
Randomization		**×**						
**Interventions**
Acupuncture			16 sessions treatment				
Sham acupuncture			16 sessions treatment				
Health control group			No acupuncture treatment				
**Assessments**
Primary outcome
Proportion of patients with ≥ 3 mean weekly CSBMs over weeks 1–4 and 5–8		**×**	**×**	**×**				**×**
**Secondary outcomes**
Proportion of patients with ≥ 1 increase of mean weekly CSBMs from baseline over weeks 1–4 and 5–8		**×**	**×**	**×**				**×**
Mean score of straining of each SBM		**×**	**×**	**×**				**×**
Mean score of stool consistency of each SBM		**×**	**×**	**×**				**×**
PAC-QOL		**×**	**×**	**×**				**×**
**Safety assessment**
Safety of acupuncture			**×**	**×**				
Adverse event			**×**	**×**				**×**
**Others**
Expectancy questionnaire		**×**						
Patients' compliance				**×**				

*CSBMs, Complete spontaneous bowel movements; SBMs, Spontaneous bowel movement; PAC-QOL, Patient Assessment of Constipation Quality of Life*.

All procedures performed in this study involving human participants will in accordance with the Declaration of Helsinki (as revised in 2013). This trial has been approved by the local ethics committee (Sichuan Regional Ethics Review of Committee on Traditional Chinese Medicine, Approval ID: 2021KL-023) and was registered on the Chinese Clinical Trial Registry (ChiCTR2100048831). This protocol is reported following the Standard Protocol Items: Recommendations for Interventional Trials (SPIRIT) (31). The flow chart of this trial is shown in Figure 1.

**Figure 1 F1:**
[figure not shown]
Flowchart of the trial design.

### Participants

#### Source of Participants

This study will be conducted in the outpatient departments of First Teaching Hospital of Chengdu University of Traditional Chinese Medicine. Recruitment will be performed mainly in the following three strategies: recruitment at anorectal and gastroenterology departments, posters in local community centers, and advertisements posted on the WeChat platform.

#### Diagnostic Criteria

According to the 2016 International Functional GI Disorders-Rome IV criteria, patients must meet the following aspects (1):

Two or more of the following must be conformed (more than 25% of defecations): a. exertion during evacuation; b. lumpy or hard stools; c. a sense of obstruction in the anus/rectum; d. sensation of incomplete evacuation; e. manual assistance is required for defecation; f. fewer than 3 mean weekly CSBMs;Loose stools rarely occur without the use of laxatives;Insufficient criteria for IBS;Criteria fulfilled for the last 3 months with symptom onset at least 6 months prior to diagnosis.

#### Inclusion Criteria

Participants meeting all the following conditions will be enrolled in this study:

Aged 18 to 60 years old;History of SCC for a minimum of 6 months before the screening visit, and the activity of symptoms last for at least 3 months;Two or fewer CSBMs per week, exertion in defecation, and lumpy or hard stools (Bristol Stool Form Scale [BSFS] ≤3) during the run-in period;No special eating habits and not accompanied by severe anxiety, depression, or other mental disorders (SAS or SDS score <75);No use of medicine for constipation during the 1 week before enrolment (except for rescue medicine), including intestinal microecological preparations, probiotics, etc.; no acupuncture treatment for constipation in the previous 1 month; no participation in any other ongoing trial;Volunteered to join this trial and signed the informed consent.

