#### Exclusion Criteria

Participants meeting any of the following aspects will be excluded:

A history of abdominal or anorectal surgery;Irritable bowel syndrome and organic or drug-induced constipation; secondary to endocrine, metabolic or neurotic constipation;Patients with severe cardiovascular, hepatic, or renal diseases or cognitive impairment, aphasia, or unable to cooperate with sample collection and treatment;Patients with other primary diseases caused by intestinal microbial disorder (diabetes, obesity, migraine, polycystic ovary syndrome, etc.);Patients during pregnancy, lactation, or with a pregnancy plan in 3 months;Patients with blood coagulation dysfunction or using anticoagulants, such as Warfarin and Heparin.

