### Intervention

The Park Sham Placebo Acupuncture Device (PSD) will be used, plus a disposable sterile acupuncture needle (length 25–75 mm, diameter 0.30 mm) for the VA group and a disposable sterile retractable blunt needle with the same size for the sham acupuncture group.

All subjects will be assigned to receive acupuncture treatments for 16 times within 4 weeks, including 5 times a week on working days for the first 2 weeks, and 3 times a week (once every other day) on working day for the last 2 weeks. The operators should be acupuncturists with a certificate to practice and at least 5 years of professional qualification.

Other medications will not be allowed, except that bisacodyl (5–10 mg) and glycerin enema (110 ml) can be used for participants who fail to have a bowel movement for 3 or more consecutive days. If the patient does not respond to bisacodyl (5–10 mg) and glycerin enema, 1–2 tablets (5–10 mg) of enteric-coated bisacodyl will be permitted (11). Furthermore, the date, specific time, dose of bisacodyl or glycerin enema using will be recorded in the defecation diary and case report form (CRF).

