### Collection of Fecal Samples

Fecal samples from 80 SCC patients will be collected at the onset and end of the treatment. Healthy volunteers will submit to only 1 stool collection (at baseline). Participants should be advised to maintain a normal diet (with no special changes compared with previous habits) in the run-in phase and avoid spicy, greasy, or probiotics-containing foods (such as yogurt) before stool samples are collected. Patients will receive a teaching video, as well as detailed written and oral instructions on how to collect feces using the Longsee fecal microbial genome protection solution kit (Guangdong Nanxin Medical Technology Co., Ltd.). Collection of two tubes of feces each time is required for the detection of intestinal microbiome and microRNAs. The collection location can be chosen at home or in the hospital according to the preferences of the participants. After collecting the inside of the middle part of the feces (about 3 g), it will be immediately transferred to the −80°C refrigerator in the hospital or temporarily stored in the 4°C refrigerators at home, and then quickly transferred to the researchers for microRNAs and gut microbiota analysis within 24 h.

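### The medicine washout is defined by indication, so patients with recent antibiotics, or probiotics taken for another reason, are eligible for a trial of gut microbiota

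*Protocol article*

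**What the plan says.** The Inclusion Criteria set one medicine washout: "No use of medicine for constipation during the 1 week before enrolment (except for rescue medicine), including intestinal microecological preparations, probiotics". It lasts one week and covers medicine taken for constipation. Microecological preparations and probiotics appear as examples within that class.

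The Exclusion Criteria come closest to the microbiota with "Patients with other primary diseases caused by intestinal microbial disorder (diabetes, obesity, migraine, polycystic ovary syndrome, etc". That item excludes diseases, not drug exposures. Neither list mentions antibiotics.

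Two other places restrict what participants may take. The Intervention section states "Other medications will not be allowed, except that bisacodyl (5–10 mg) and glycerin enema (110 ml) can be used". The section on fecal sample collection asks participants to "avoid spicy, greasy, or probiotics-containing foods (such as yogurt) before stool samples are collected".

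The Introduction, in arguing for the microbiota hypothesis, reports that "acupuncture was found to be lesser effective when the intestinal microbial community was dysregulated by antibiotics".

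**The concern.** The second and third objectives concern the gut microbiota, fecal miRNAs and their relation to symptom improvement. For those objectives, the pre-entry exposures that matter are those that alter the microbiota, whatever they were taken for. The washout sorts exposures by indication, so it removes a probiotic taken for constipation and admits the same probiotic taken for another reason. It does not reach antibiotics at all, although the protocol itself names antibiotic disturbance as something that weakens the effect under study.

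Two kinds of analysis are affected, in different ways:

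- **Patients versus healthy volunteers at baseline.** This comparison is not randomised, and the matching is described only in terms of demographic characteristics such as age and sex. If recent antibiotic use differs between the groups, its effect is mixed with that of constipation. The miRNA section then looks for efficacy biomarkers only among candidates from this comparison, so an artefact at baseline can decide which candidates go forward.
- **Verum versus sham, and the tripartite network correlations.** A microbiota recovering from antibiotics may change over the four treatment weeks in either arm. This adds variation unrelated to treatment and may dilute the effect. The network analysis accepts correlations at an uncorrected 5% level, so it offers little filter.

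**Working it through.** The plan states no figure on this point, so there is nothing to reproduce. The finding rests on reading the provisions together; the arithmetic only illustrates its possible scale.

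**1. Does any provision keep out a patient who finished antibiotics the day before enrolment?**

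| Provision | What it covers | Closes the gap? |
|---|---|---|
| Inclusion Criteria, washout | Medicine for constipation, one week | No: antibiotics are not medicine for constipation |
| Exclusion Criteria | Diseases linked to microbial disorder; anticoagulants; other conditions | No: no antibiotic exposure named |
| Intervention, other medications | Stated with the treatment rules | No: not worded to reach back before enrolment |
| Collection of Fecal Samples | Foods before sampling | No: no drug named |

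Table 1 places the microbiota and miRNA analyses in the Week −1 column. On that schedule the run-in gives no clearance time before the baseline sample either.

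**2. Illustration for the patient–volunteer comparison.** Input from the protocol: 40 per group (40 volunteers, set against one arm's worth of patients for simplicity). Assumptions, not in the documents: a share f of patients and no volunteers recently exposed, and a shift of D standard deviations in a microbiota feature among the exposed. Normal approximation, two-sided 5% test.

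- Spurious difference: d = f × D
- Standard error: √(2/40) = 0.224 SD
- Rejection rate with no true difference: Φ(d/0.224 − 1.96) + Φ(−d/0.224 − 1.96)

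| f | D | d (SD) | Rejection rate per feature |
|---|---|---|---|
| 5% | 0.5 | 0.025 | 5.1% |
| 5% | 1.0 | 0.05 | 5.6% |
| 10% | 0.5 | 0.05 | 5.6% |
| 10% | 1.0 | 0.10 | 7.3% |
| 20% | 0.5 | 0.10 | 7.3% |
| 20% | 1.0 | 0.20 | 14.5% |

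For the last row: 0.20/0.224 = 0.894, and Φ(−1.066) + Φ(−2.854) = 0.143 + 0.002 = 0.145.

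**3. Illustration for the randomised arms.** Number exposed in each arm ~ Binomial(40, f), independent; f is again assumed.

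| f | Expected per arm | P(arms differ by ≥3) | P(arms differ by ≥4) |
|---|---|---|---|
| 5% | 2 | 19% | 7% |
| 10% | 4 | 35% | 19% |
| 20% | 8 | 48% | 33% |

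These are chances of imbalance in either direction. The cut-offs of 3 and 4 are arbitrary, and the figures do not translate into a bias in any outcome.

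**The case against.** The best reply is that much of this is already handled or small. Probiotics are named in the washout, probiotic foods are barred before sampling, and "Other medications will not be allowed" appears under Intervention. Randomisation balances prior antibiotic use in expectation. The Introduction's remark on antibiotics is one sentence without population, timing or effect size, and applying it to a patient who has finished a course is extrapolation. At the low end of the illustration the inflation, 5.1% against 5%, is negligible.

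Most of this stands as a limit on degree. It leaves the gap open: pre-enrolment antibiotics, and probiotics taken for another reason, remain admissible, and randomisation does nothing for the comparison with volunteers. Nor is this a detail that an article would leave to a fuller protocol. The washout is printed and its limit is explicit.

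Three stronger readings are tempting and are not supported.

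- **Systematic bias between verum and sham.** A reader might infer this from the exposure. Allocation is random, so the expected difference in exposure is zero.
- **A compromised sham blind.** The acupuncture criterion, "no acupuncture treatment for constipation in the previous 1 month", is also limited by indication, so a patient recently needled for another complaint is eligible. But recognising a non-penetrating needle depends on having been needled at all, whatever the complaint. A patient treated for constipation two months earlier is eligible and just as experienced. The documents give neither the share of such patients nor a recognition rate.
- **Carry-over from earlier acupuncture.** The Introduction says "The effects of acupuncture could accumulate with 4-week treatments and persist throughout the 4-week follow-up". The one-month window covers that reported period; calling it too short assumes an effect beyond what is reported. The run-in requirements on bowel frequency, straining and stool form would also tend to screen out a patient still benefiting.

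**Conclusion.** The point holds for microbiota-altering exposures before entry. As written, the criteria admit patients with recent systemic antibiotics or with probiotics taken for a reason other than constipation, which sits badly with the protocol's own statement about antibiotics.

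The main consequence is possible confounding of the baseline patient–volunteer comparison and of the biomarker pool drawn from it. For verum versus sham and for the network correlations, the consequence is noise, dilution and chance imbalance.

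The size cannot be derived from the documents. The range of 5.1% to 14.5% per feature assumes 5–20% of patients and no volunteers exposed, and a shift of 0.5–1.0 SD. Equal exposure in both groups would remove the confounding and leave the added noise. The change is worth making before enrolment because it is cheap and protects the second and third objectives.

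**What to change.** Reconcile the Inclusion Criteria with the Introduction by defining the washout by exposure:

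- No systemic antibiotics, and no probiotic or microecological preparation for any reason, within a fixed window before the baseline stool sample. The investigators should choose and justify the length; the documents give no basis for a particular one.
- Apply the same criterion to the healthy volunteers, so that the two groups in the baseline comparison are selected alike.
- Record antibiotic and probiotic exposure at screening for everyone, so that any remaining use can be described.

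The cost is a change to one criterion, its extension to the volunteers and a screening question. The downside is small: a few recently exposed candidates are deferred or screened out.
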